## Abstract

**Background:**

Symptoms associated with osteoarthritis of the knee result in decreased function, loss of working capacity and extensive social and medical costs. There is a need to investigate and develop effective interventions to minimise the impact of and even prevent the progression of osteoarthritis. Aquatic exercise has been shown to be effective at reducing the impact of osteoarthritis. The purpose of this article is to describe the rationale, design and intervention of a study investigating the effect of an aquatic resistance exercise intervention on cartilage in postmenopausal women with mild knee osteoarthritis.

**Methods:**

A minimum of 80 volunteers who meet the inclusion criteria will be recruited from the local population through newspaper advertisements. Following initial assessment volunteers will be randomised into two groups. The intervention group will participate in a progressive aquatic resistance exercise program of 1-hour duration 3 times a week for four months. The control group will be asked to maintain normal care during this period. Primary outcome measure for this study is the biochemical composition of knee cartilage measured using quantitative magnetic resonance imaging; T2 relaxation time and delayed gadolinium-enhanced magnetic resonance imaging techniques. In addition, knee cartilage morphology as regional cartilage thickness will be studied. Secondary outcomes include measures of body composition and bone traits using dual energy x-ray absorptiometry and peripheral quantitative computed tomography, pain, function using questionnaires and physical performance tests and quality of life. Measurements will be performed at baseline, after the 4-month intervention period and at one year follow up.

**Discussion:**

This randomised controlled trial will investigate the effect a progressive aquatic resistance exercise program has on the biochemical composition of cartilage in post-menopausal women with mild knee osteoarthritis. This is the first study to investigate what impact aquatic exercise has on human articular cartilage. In addition it will investigate the effect aquatic exercise has on physical function, pain, bone and body composition and quality of life. The results of this study will help optimise the prescription of aquatic exercise to persons with mild knee osteoarthritis.

**Trial Registration:**

ISRCTN65346593

## Background

Osteoarthritis (OA) of the lower limb is a leading cause of decreased function and quality of life [1]. It has been estimated that the prevalence of symptomatic OA of the knee is between 7-33% with an increase in prevalence with age and is the most common site of symptomatic OA [2-6]. Early signs of OA in articular cartilage, which is constituent for the initiation and progression of OA, are characterised with loss of proteoglycans, breakdown of the collagen matrix and increased water content [7]. As the disease progresses there is fibrillation of the cartilage, changes in the subchondral bone, formation of osteophytes and thickening of the synovium [8-11] and as such OA is considered a whole joint disease. These modifications within the joint lead to the gradual development of clinical symptoms such as stiffness, decreased range of motion and pain [12] which cause a decrease in joint proprioception [13] and inhibits muscle activation [14,15] leading to a decrease in activity. This disuse results in a lowering of aerobic capacity, muscle strength and muscle mass and ultimately a decrease in functional capacity and increased dependence [16,17]. Additionally, reduced muscle strength is a risk factor for future pain [17], self-reported knee instability [18] and increased risk of falling [19]. These in combination cause the extensive social and medical costs to society as a direct or indirect result of OA.

Although there is no known cure for OA the disease-related factors such as impaired muscle function and reduced aerobic fitness can be improved and maintained with therapeutic exercise [20,21]. Previous systematic reviews have demonstrated that exercise has positive effects on pain and function for people with symptomatic OA of the knee [21-23] and is recommended as one of the primary non-pharmaceutical treatment modalities in current OA guidelines [24-29]. Exercising in water is also strongly recommended in these guidelines. There is evidence to suggest that therapeutic aquatic exercise has a short term positive effect on pain and function in persons with OA of knee and/or hip similar to that of land training [30,31]. There is good evidence to support the use of strength exercises in the management of symptoms resulting from OA [32] however, there is conflicting evidence that therapeutic aquatic exercises can improve strength of lower limb muscles in persons with OA [33-40]. It is thought that the benefits from aquatic exercise are primarily a result of the decreased effects of gravity. Buoyancy reduces compressive and shear forces on joints and thus offers a comfortable training medium for patients with OA [41].

Previously, one restriction in OA research was the lack of non-invasive *in vivo* techniques to quantify the structure and acute changes in cartilage. Advances in magnetic resonance imaging (MRI) have made mapping of the articular cartilage and loading related changes possible [42]. The “delayed Gadolinium Enhanced MRI of Cartilage” (dGEMRIC) technique utilizes a paramagnetic contrast agent gadolinium (Gd-DTPA^2-^) to detect early reduction of glycosaminoglycan (GAG) from the matrix, a phenomenon considered to represent the onset of the degenerative process of cartilage [43]. Measurement of T2 relaxation time, sensitive to degeneration of tissue collagen and the orientation of collagen fibres in the extracellular matrix, has been developed to detect early degeneration or senescent changes of cartilage [44,45]. In addition, the assessment of morphological properties from three-dimensional MRI measurements enables assessment of tissue changes at a macroscopic scale [46] which have been found to be reliable, responsive and valid methods for mapping the volumetric data of articular cartilage [47-49].

There is still a lack of evidence that human cartilage can adapt to mechanical loading in a similar way to other tissues such as bone and muscle. Animal studies have suggested that physical exercise can improve tissue integrity by increasing the GAG content and indentation stiffness in load bearing cartilage [50,51]. In a cross-sectional study Tiderius et al. [52] concluded, based on dGEMRIC measurements, that GAG content was higher in regularly exercising individuals than in sedentary subjects. Additionally, observations by Teichtahl et al. [53] suggest that vigorous physical activity is associated with a reduced rate of patella cartilage volume loss in asymptomatic subjects. To date, only one randomised intervention study investigating the direct effect of exercise on biochemical composition of human cartilage [54] has been published. Roos et al. [54] reported a positive effect of a moderate four months exercise on the GAG content, measured with dGEMRIC in subjects with high risk of knee OA. Another study by Cotofana et al. [55] provides no evidence that a 3-month exercise intervention in untrained middle-aged women can significantly alter cartilage morphology in the knee joint. Furthermore, the optimal type or intensity of exercise for improvement in cartilage is not known and longitudinal effects of training are needed to determine the exercise response once OA is established. In particular, there are no studies investigating the effect non-impact training such as therapeutic aquatic exercise has on the structures related to and progression of OA in the knee joint.

Therefore we plan to investigate the effects of an intensive aquatic resistance exercise program on the biochemical composition and morphology of the knee cartilage as well as its effect on physical function in postmenopausal women with mild knee osteoarthritis. In addition, we plan to discover if the possible benefits of exercise on cartilage, symptoms and physical function can be maintained one year after training period.

The purpose of this article is to describe the rationale, design and intervention of a study investigating the effect an aquatic resistance exercise intervention has on the cartilage in postmenopausal women with mild knee osteoarthritis.

## Methods and design

### Study design

The design of this study will be a 4-month randomised controlled exercise intervention study (RCT) with a 16 month follow up (Trial registration: ISRCTN65346593). After baseline measurements the voluntary participants will be randomly assigned into the two arms of the study, an aquatic resistance strength training group and a control group. All the outcome measurements will be performed at baseline, after the 4-month intervention and at follow up 12 months after cessation of training.

### Participants and selection criteria

Volunteer postmenopausal women, between the ages of 60–68 year-old, will be recruited through a series of local newspaper advertisements and will be gathered from the county of Central Finland which has a population of approximately 275 000. Inclusion eligibility, (see below), will be initially assessed using a structured telephone interview. The telephone questionnaire includes questions concerning degree of knee pain, current level of physical activity and past medical history.

Suitable participants will be taken forward and they will undergo weight bearing x-ray imaging of both knees. An experienced radiologist and orthopaedic physician will assess the images grading the degree of OA in the tibiofemoral and patellofemoral joints using the Kellgren-Lawrence grading (K/L 0-IV) [56]. Those participants who have a KL score of I (possible osteophytes) or II (definite osteophytes, possible joint space narrowing), will be included in the next stage of eligibility assessment and undergo a medical and physiotherapy screening. At this point any possible physical or medical limitations to full participation in the intervention will be assessed e.g. severely restricted joint range of movement (ROM), excessive laxity of knee joint, possible physical disabilities and abnormalities found from resting echocardiogram.

Subjects will be excluded if they have at least one of the following criteria; BMI > 34, resting pain in knee VAS > 50/100, known loose particles in knee joint, acute inflammation in knee joint, knee intra-articular steroid injection in previous 3 months or oral steroid medication treatment in the previous 12 months, undergoing treatment for osteoporosis or T-score for femoral neck bone mineral density (BMD, g/cm^2^) lower than −2.5 i.e. indicating osteoporosis as measured with DXA [57-59], previous cancer or radiotherapy, suffer from type I or II diabetes, cardiac disease, diagnosed rheumatic disease (other than OA), undergone surgical procedure to knee (excluding menisectomy or arthroscopy if over 12 months ago) or joint replacement surgery in lower limbs.

Additional exclusion criteria are problems that would prevent MRI imaging, including electronic or magnetic implants e.g. pace maker, metal within body e.g. internal bone fixations, artificial aortic heart valve, metal particles in eyes, large tattoos on lower limb, claustrophobia or possible allergy to the contrast medium. Further, fasting blood samples will be taken to analyse Krea to ensure kidney function for normal removal of contrast medium from the body. All those participants fulfilling all the inclusion criteria will be included into the study and undergo the baseline measurements. Figure 1 shows the flow chart describing the selection and measurement procedure for the whole study.

**Figure 1 F1:**
[figure not shown]
Flow chart showing enrolment, allocation and follow-up measurements.

### Sample size

The sample size and power calculations have been estimated for the primary end points of this study, i.e. the dGEMRIC and T2 variables. Based on data from Roos et al. [54] and Tiderius et al. [55] it is estimated that 30 subjects are needed, at 80% power, to detect a mean ± SD difference of 40 ± 40 msec in the dGEMRIC between groups [54]. It is estimated that dropout rate will be about 20% at the 16 months follow up, consequently at least 70 subjects will need to be recruited.

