### Randomisation and blinding

The subjects will be randomly allocated into either of the two arms of the study by an external statistician blinded for the intervention and study participants and will only be provided with a randomisation number for each participant and severity of OA in knee according to x-ray classification. A computer generated block randomisation of size of ten, stratified according to Kellgren-Lawrence grading 1 and 2, will be used to ensure equal distribution of severity of OA within each group and equal group size.

As with all exercise intervention studies blinding of the subject from the intervention is not possible. Researchers (BW, MM, AH) will be blinded to the allocation of groups as well as blinded from the interventions and measurement except for pQCT (MM) and DXA (BW) measurements. Due to practical limitations the physical therapists providing the intervention will also be performing the physical performance measurements. All statistical analyses will be completed by a statistician (HK), who is blinded to the participants and measurements.

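### The two steps of the sample-size statement need different meanings of the 30 subjects, and the recruitment minimum is 70 in one place and 80 in another

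*Protocol article*

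**What the plan says.** The Sample size section of the protocol article makes its calculation in two steps.

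- Required number: "30 subjects are needed, at 80% power, to detect a mean ± SD difference of 40 ± 40 msec", for dGEMRIC and between the two groups.
- Allowance for loss: "dropout rate will be about 20% at the 16 months follow up, consequently at least 70 subjects will need to be recruited".

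The section gives no significance level, sidedness or test. It does not say whether the 30 are the whole trial or one arm. Allocation is 1:1: the Randomisation and blinding section says that the blocked, stratified scheme "will be used to ensure equal distribution of severity of OA within each group and equal group size".

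The Methods paragraph of the abstract gives another recruitment figure: "A minimum of 80 volunteers who meet the inclusion criteria will be recruited". Nothing in the article connects the 70 with the 80.

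**The concern.** The second step is presented as a consequence of the first, so a reader should be able to go from 40 ± 40 ms to 30, and from 30 to 70, without changing what 30 means. That is not possible. If 30 is a total, 70 is almost twice what the dropout allowance requires. If 30 is per arm, the stated 80% is not the power of the design.

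The practical stake is the rule for when recruitment may stop. Two floors are given, and the derivation does not show which one the calculation supports. Each participant also has a 3-hour imaging session with a double dose of contrast at each of three time points, so the number enrolled should have a justification that can be traced. And a reader of the eventual results needs to know what difference the trial was built to detect. The stated 80% power for 40 ms does not describe a trial of 70 or 80 women.

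**Working it through.** **Inputs from the article.** Difference 40 ms, SD 40 ms, power 80%, dropout about 20%, 1:1 allocation, recruitment of at least 70 (Sample size) or at least 80 (abstract).

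**Assumptions.** Two-sided 5% unless another level is named, a comparison of two independent means, and 40 ms as the SD of the quantity compared. The standardised effect is then 40/40 = 1.0.

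**Step 1: from 40 ± 40 ms to 30**

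Normal formula: n per arm = 2 × (1.960 + 0.842)² / 1.0² = 15.7, rounded up to 16, so 32 in total. Two-sample t test: 16.7, rounded up to 17, so 34 in total.

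| Reading of 30 | Per arm | Power, normal | Power, t test |
|---|---|---|---|
| Total | 15 | 78.2% | 75.3% |
| Per arm | 30 | 97.2% | 96.8% |

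As a total, 30 is close to the required 32–34. As a per-arm number it is nearly twice the 16–17 needed. A stricter level does not rescue the per-arm reading: the normal formula gives 20 per arm at two-sided 2.5% and 24 at two-sided 1% (t test: 21 and 26). To need 30 per arm at 80% power, the SD would have to be about 55 ms instead of the stated 40.

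**Step 2: from 30 to 70**

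Two inflation rules are in use: N/(1 − 0.2), which preserves the required number of completers, and N × 1.2, a common shortcut that falls slightly short.

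| Reading of 30 | N before loss | N/0.8 | N × 1.2 |
|---|---|---|---|
| Total | 30 | 37.5, so 38 | 36 |
| Per arm | 60 | 75 | 72 |

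As a total, neither rule comes near 70. As a per-arm number, the shortcut comes within 2 of 70, and the exact rule gives 75.

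**Both steps together**

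| Reading of 30 | Fits 40 ± 40 ms at 80%? | Leads to 70? |
|---|---|---|
| Total | Approximately | No (36–38) |
| Per arm | No (about 97%) | Approximately (72, or 75) |

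Step 1 needs the first reading and step 2 needs the second.

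**What the two recruitment minimums deliver (t test, SD 40 ms, 20% loss)**

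| Recruited | Completers | Per arm | Power for 40 ms | Difference detectable at 80% power |
|---|---|---|---|---|
| 70 | 70 × 0.8 = 56 | 28 | 95.7% | 30.5 ms |
| 80 | 80 × 0.8 = 64 | 32 | 97.6% | 28.5 ms |

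Seventy recruits therefore leave 28 per arm, 2 short of 30 per arm if that was the intention. Eighty leave 32.

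**The case against.** **The figures are within ordinary conventions.** Alpha, sidedness and test are unstated, so a reader might infer too much by saying that 30 cannot be reproduced at all. It can, approximately and as a total: the normal formula gives 32, a two-sided t test 34 and a one-sided 5% t test 28. Likewise 70 is within 2 of 60 × 1.2. This stands, and it rules out any claim that either step fails on every reading. It does not repair the chain, because the two approximate matches use different meanings of the same number.

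**The two minimums are compatible.** Both are floors, and recruiting 80 satisfies both. That is true, but a team relying on the Sample size section may stop at 70 while the abstract requires 80. The article does not say which governs.

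**Nothing is lost in power.** A reader might infer that the trial is too small, or that it enrols far more women than it needs. The documents support neither as a finding. On the stated SD, even 70 recruits give about 96% power for 40 ms. The charge of over-enrolment needs 30 to be a total, the charge of falling short needs it to be per arm, and the two cannot be combined.

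**T2.** The section says that the calculations were "estimated for the primary end points of this study, i.e. the dGEMRIC and T2 variables", yet prints inputs only for dGEMRIC. A reader might infer that T2 was never powered. The article does not show that: it condenses a fuller protocol, where the T2 inputs may stand. The same applies to whether the 40 ms is the SD of a single value or of the change.

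**The reference.** The second source is cited as [55], which the Background uses for a 3-month exercise study of cartilage morphology; there, the cross-sectional dGEMRIC study is [52]. This is a clerical slip and affects no figure.

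**Conclusion.** The point holds as an inconsistency in the derivation. As written, the required number, the stated power and the recruitment target cannot be read as one calculation. With 30 as a total, the target should be 36–38 instead of 70; with 30 as per arm, the power is about 97% instead of 80%. Separately, the recruitment minimum differs by 10 women between the abstract and the Sample size section.

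The power figures rest on a two-sided 5% level, which the article does not state, and on 40 ms being the SD of the quantity compared. If the investigators had a larger SD in mind, near 55 ms, 30 per arm would match 80% power; the text would then need that SD. The conflict between 70 and 80 depends on no assumption.

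It should be corrected because the stated sample size and power are what the trial will be judged against. It does not put the dGEMRIC comparison at risk for the stated 40 ms effect.

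**What to change.** Restate the Sample size section as one chain: significance level and sidedness, the difference and SD, the number needed marked as per arm or total, the dropout inflation, the recruitment minimum, and the power that this minimum delivers. Use the same minimum in the abstract.

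The investigators must supply their own alpha and choose the minimum. With two-sided 5% and a t test, a consistent version would be:

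- 17 per arm (34 evaluable) give 80% power for 40 ± 40 ms.
- If 80 is the minimum, 20% dropout leaves 32 per arm: about 98% power for 40 ms, or 80% power for 28.5 ms.
- If 70 is kept, 28 per arm remain: about 96% power for 40 ms, or 80% power for 30.5 ms.

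The reference number of the second source can be corrected at the same time.

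The cost is wording only. Neither the design nor the analysis changes. Adopting 80 in both places adds no one beyond what the abstract already promises.

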### Randomisation and blinding

The subjects will be randomly allocated into either of the two arms of the study by an external statistician blinded for the intervention and study participants and will only be provided with a randomisation number for each participant and severity of OA in knee according to x-ray classification. A computer generated block randomisation of size of ten, stratified according to Kellgren-Lawrence grading 1 and 2, will be used to ensure equal distribution of severity of OA within each group and equal group size.

As with all exercise intervention studies blinding of the subject from the intervention is not possible. Researchers (BW, MM, AH) will be blinded to the allocation of groups as well as blinded from the interventions and measurement except for pQCT (MM) and DXA (BW) measurements. Due to practical limitations the physical therapists providing the intervention will also be performing the physical performance measurements. All statistical analyses will be completed by a statistician (HK), who is blinded to the participants and measurements.

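### A single published block size of ten in each Kellgren-Lawrence stratum could let up to about 15–17% of assignments be deduced if women are allocated one at a time; undisclosed varying block sizes are a cheap improvement

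*Protocol article*

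**What the plan says.** All quotes are from the protocol article.

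- **Block size and strata** (Randomisation and blinding): "A computer generated block randomisation of size of ten, stratified according to Kellgren-Lawrence grading 1 and 2, will be used". The stated purpose is "to ensure equal distribution of severity of OA within each group and equal group size", which with two arms implies 5:5 within each block.
- **Who allocates** (same section): the allocation is made "by an external statistician blinded for the intervention and study participants and will only be provided with a randomisation number for each participant", together with the x-ray grade.
- **Blinding** (same section): "As with all exercise intervention studies blinding of the subject from the intervention is not possible". On the therapists: "Due to practical limitations the physical therapists providing the intervention will also be performing the physical performance measurements".
- **Timing** (Study design): "After baseline measurements the voluntary participants will be randomly assigned into the two arms of the study". Whether this happens woman by woman or in batches is not stated.
- **Steps before allocation** (Participants and selection criteria): women with grade I or II on x-ray "will be included in the next stage of eligibility assessment and undergo a medical and physiotherapy screening". The stratum is therefore fixed before screening and baseline testing.
- **Delivery** (Intervention): pool training runs in groups of 6–8.

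**The concern.** A fixed block size that is known to study staff makes the end of each block predictable. Concealing the list with an external statistician does not prevent this, because the deduction uses assignments already made and does not need the list.

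Two features make the question worth asking here. The therapists see who trains, and they also take the physical performance measurements, which are among the outcomes measured at baseline. In addition, judgement enters before allocation: screening looks for limitations to full participation, and the strength, power and walking tests depend on effort. Someone who could foresee the next assignment might influence whether or when a woman is entered (selection bias), or how her baseline tests are coached or scored (measurement bias). In a trial of 70–80 women, a few steered entries could matter.

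**Working it through.** The article gives no predictability figure to reproduce, so the exposure is derived from its stated design.

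**Inputs.** Block size 10, two arms of equal size (m = 5 per arm per block) and two strata, all from Randomisation and blinding. Total recruited: at least 70 (Sample size) or a minimum of 80 (Abstract, Methods). The split between strata is not given; 30% and 50% in one stratum were assumed.

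**1. Certain assignments, complete block.** An assignment is certain once one arm has used its m places. The expected number of certain assignments is the expected length of the final run of one arm: m/(m+1) for each arm, so 2m/(m+1) in all.
- m = 5: 2 × 5/6 = 1.67 of 10, or 16.7%. Enumerating all 252 possible blocks gives the same value.
- Other fixed sizes, for comparison: 33.3% for 4, 25.0% for 6, 20.0% for 8, 14.3% for 12.

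**2. Incomplete last blocks.** Recruitment will usually stop part-way through a block. By simulation with two strata:
- N = 80: about 12.0 women, 15.0–15.1%.
- N = 70: about 10.4 women, 14.8%.
- If each stratum held exactly 40 women (four full blocks), the figure would be 80 × 0.167 = 13.3.

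The results for the two assumed stratum splits are almost identical.

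**3. Best guessing.** An observer who always guesses the arm with fewer places used is right on average m + 2^(2m−1)/C(2m,m) − 0.5 times per block:
- 5 + 512/252 − 0.5 = 6.53 of 10, or 65.3%; 80 × 0.653 = 52.2 women, against 40 by chance.

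**4. Effect of batches.** Steps 1–3 assume that every earlier assignment is visible before the next woman is allocated. If women are allocated in batches and only earlier batches are visible (N = 80, two equal strata), the certain share is:

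| Batch size | Certain assignments |
|---|---|
| 1 | 15.1% |
| 8 | 5.5% |
| 16 | 3.0% |
| 40 | 0.7% |
| 80 (all at once) | 0% |

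**5. Effect of varying sizes.** With blocks of 8, 10 and 12 in random order, two strata of 40, and an observer who knows the set of sizes but not their order, simulation gives:
- certain: about 1.2 of 80 (1.5%), against about 13.3 for fixed tens under the same assumptions;
- correct best guesses: about 51.5–51.7 of 80 (64–65%), against 52.2.

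The gain comes only from secrecy. If each block's size were known, the average would be (1.600 + 1.667 + 1.714)/3 = 1.66 per block of mean size 10, or 16.6%, the same as now.

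**The case against.** The case against is substantial.

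- **The conditions are not in the text.** A reader might infer that therapists who watch the pool can know one assignment in six. The article does not support that. Pool attendance shows only the training arm. To know that the next assignment is forced, an observer also needs the controls already allocated, the entry order, each woman's grade and where the current block began. Nothing says that pool staff hold these, or that they knew the block size during recruitment. Groups of 6–8 make batch starts plausible.
- **No enrolling role is described.** Pool therapists are not said to screen, enrol or order the entry of women. Allocation follows each woman's own baseline and is made by an external statistician. A reader might infer selection bias between the arms; the article shows at most an opportunity for it.
- **The primary outcomes are remote.** They are quantitative MRI measures. The tests that unblinded therapists score are secondary outcomes.
- **Ten is not a poor choice of fixed size.** It is less predictable than 4, 6 or 8.
- **Release logistics belong in the full protocol.** A journal article commonly leaves them there, so silence on batching is not a fault in itself.

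All of this stands, and it limits the point to a conditional upper bound. What remains is that the article does state a rule, one fixed and disclosed size, and that external allocation does not protect against deduction from past assignments. Staggered entry is also plausible: recruitment uses a series of advertisements, and each imaging session lasts 3 hours.

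**Conclusion.** The concern holds as a conditional upper bound. Up to about 15–17% of assignments (roughly 12 of 80 or 10 of 70) could be known in advance if allocation is strictly sequential, runs alongside screening or baseline testing of other women, and is watched by someone who knows the block size, order, grades and all earlier assignments. The documents neither state nor exclude this. With batches of 8 the bound is about 5.5%, and with a single allocation of all women it is zero.

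A reader might also infer that any batch release abolishes foreknowledge. It does not, since small batches still leave some assignments forced; only allocating everyone together does. Nor do varying block sizes make the sequence unpredictable, because best-guess accuracy stays near 64–65%.

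This is a low-cost improvement of modest priority. It is not an error that invalidates the primary MRI comparison.

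**What to change.** 1. Keep the external statistician and the Kellgren-Lawrence strata. Replace the fixed block of ten with randomly varying sizes (for example 8, 10 and 12 in random order), held only by that statistician and not disclosed until recruitment closes.
2. Where scheduling allows, release allocations only when eligibility and baseline are complete for as large a batch as possible, ideally all women at once. State in the protocol which applies. If all women are already allocated together, saying so answers the concern and step 1 is not needed.

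**Cost.** A new computer-generated list and one or two sentences of text, with no extra women, visits or staff. Arm sizes may differ by one or two more women per stratum; the largest possible imbalance in a stratum is half the open block, so it rises from 5 to 6. Batch release may slightly delay some starts.
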